### Randomization

Randomization to treatment arms will be performed at a 1:1 ratio. Randomization will be performed via a centralized system with an Internet-based tool. Patients will be randomized dynamically. The permuted block sizes will randomly vary between 2, 4, and 6.

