### Blinding

Due to the physical differences between the treatment regimens, it is not possible to blind either participant or physician to the treatment. To address issues of blinding, wound photo documentation will be obtained during the trial and confirmation of wound closure will be assessed via blinded assessment of photos by independent observers, which will serve as the method of primary endpoint analysis.

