### Type of analysis

The primary efficacy parameter, time to complete wound closure, will be compared between the two treatment groups using a log-rank test. In addition, as a supportive analysis, a Cox proportional hazards regression will also be used in order to assess if there is a difference between treatment groups while accounting for the effect of study center and wound size (appropriate baseline and medical history parameters will also be considered). The secondary efficacy parameter, incidence of complete wound closure, will be analyzed using a chi-squared test comparing the two treatment groups. As a supportive statistical analysis, logistic regression will also be implemented. The logistic regression will include treatment, study center, and wound size. Reduction in wound area (cm^2^) and wound volume (cm^3^) will be assessed using a three-factor (treatment group, study center, and time) analysis of covariance with baseline wound area (or volume) recorded at baseline to be used as a covariate. One planned interim analysis will be performed when 250 study participants have completed the first phase of the study. The interim analysis will validate the assumptions made for the study sample size calculation and will determine if sample size re-estimation is warranted.

The results of the SAWHI-V.A.C.®-study will be analyzed by the intention-to-treat (ITT) approach. The ITT analysis population will include all randomized participants who have a valid baseline and at least one valid post baseline wound assessment (examination). For the ITT analysis population, participants will be assigned to the treatment group based on the randomization schedule, regardless of the treatment actually received. For the analysis of the primary efficacy endpoint, missing values will be incorporated as censored values. For secondary endpoints, methods for imputing missing or partially missing data will be used as appropriate. The last observation carried forward (LOCF) method will be used for the analysis of the endpoints ‘incidence of wound closure’; ‘recurrence’ and ‘reduction of wound size’ in case of study determination or death.

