As a secondary approach, a per protocol (PP) analysis will be performed without patients with any protocol deviations. Violations of inclusion and exclusion criteria; changes of randomized therapy; the use of concomitant therapies or procedures deviating from the clinical standard wound treatment or with investigational character (for example, use of hyperbaric oxygen therapy) and dressing changes not performed as recommended to be performed every 48 to 72 hours (no fewer than three times per week) will be considered as protocol deviations. Furthermore, during analysis, concomitant therapies or procedures will be evaluated regarding its impact to directly affect wound healing or the ability to observe wound healing.

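### The set labelled ITT leaves out randomised participants who lack a valid baseline or post-baseline wound assessment, so the main analysis of this open-label trial is a modified ITT

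*Protocol article*

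**What the plan says.** Under Type of analysis, the protocol article states that the trial results "will be analyzed by the intention-to-treat (ITT) approach". The next sentence defines the set: "The ITT analysis population will include all randomized participants who have a valid baseline and at least one valid post baseline wound assessment". Within that set, "participants will be assigned to the treatment group based on the randomization schedule, regardless of the treatment actually received".

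Three other statements bear on the point:

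- **Primary test.** The primary parameter, "time to complete wound closure, will be compared between the two treatment groups using a log-rank test". On missing data: "For the analysis of the primary efficacy endpoint, missing values will be incorporated as censored values".
- **Secondary test.** Incidence of closure is compared with a chi-squared test. Last observation carried forward is used for incidence when a participant leaves the study or dies.
- **Role of the sets.** "As a secondary approach, a per protocol (PP) analysis will be performed without patients with any protocol deviations". The restricted set is therefore the main one, and no analysis of all randomised participants is described.

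Under Blinding, the article says that "it is not possible to blind either participant or physician to the treatment". Blinded readers assess the wound photographs.

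**The concern.** The label and the definition disagree. Having a post-baseline assessment is an event after randomisation, and here it happens after everyone involved knows the arm. A participant who withdraws on learning the allocation, or who dies or is lost before the first assessment, leaves the analysis, and the chance of that can differ between arms. Blinded photograph reading protects how closure is classified. It does not protect who enters the set.

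If the participants lost are mostly ones who would not have closed, and more are lost from one arm, that arm's closure rate is overstated. The study objectives section says the trial is designed to meet all quality requirements of the German assessment bodies. For that purpose, a restricted set that carries the ITT name is an avoidable weakness.

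**Working it through.** **1. The plan's own sample size.** Inputs from Determination of sample size: 50% against 62.5% closure, 80% power, α = 0.05 or 0.048 (two-sided assumed, because that reproduces the figures).

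n per arm = [z(α/2)·√(2·p̄·q̄) + z(β)·√(p₁q₁ + p₂q₂)]² / d², with p̄ = 0.5625 and d = 0.125

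- α = 0.05: (1.960·0.7016 + 0.8416·0.6960)² / 0.015625 = 246.1, which is 247 rounded up (stated 246).
- α = 0.048: (1.977·0.7016 + 0.8416·0.6960)² / 0.015625 = 249.1, which is 250 rounded up (stated 249, or 498 in total).
- 10% loss: 498/0.9 = 554 rounded up, or 498·1.1 = 548 (stated 550).

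The sizing stands. The 10% allowance covers lost precision, not selective loss.

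**2. Which test does the exclusion touch?**

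- *Log-rank, no post-baseline data.* Under the stated censoring rule, such a participant is censored at Day 0 and belongs to no risk set. The contribution to observed events, expected events and variance is zero. The statistic is the same with or without that person.
- *Log-rank, some follow-up but an assessment judged not valid.* Here the definition removes real time at risk, so the test changes.
- *Chi-squared on incidence.* Removing k non-closers from n changes the rate from x/n to x/(n − k). The definition acts directly.

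**3. Size on the closure-rate scale.** Assumptions: 275 per arm (550/2), true closure 50% in both arms, two-sided α = 0.048, all excluded participants are non-closers. The exclusion rates are assumed because the article gives none.

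With a fraction e excluded from an arm, the apparent rate is 0.5/(1 − e) on 275(1 − e) participants. For 5% against 0%:

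- rates 0.5/0.95 = 0.5263 and 0.5000, difference 0.0263
- pooled rate 275/536.25 = 0.5128; null SE 0.04318; unpooled SE 0.04317
- rejection = Φ[(0.0263 − 1.9774·0.04318)/0.04317] + Φ[(−0.0263 − 1.9774·0.04318)/0.04317] = 0.0856 + 0.0048 = 9.0%

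| Excluded (arm A / arm B) | Spurious difference, points | Type I error |
|---|---|---|
| 2% / 0% | 1.0 | 5.4% |
| 5% / 0% | 2.6 | 9.0% |
| 10% / 0% | 5.6 | 24.0% |
| 10% / 5% | 2.9 | 9.8% |
| 5% / 5% | 0 | 4.8% |

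**4. Size on the log-rank scale.** Simulated with 249 per arm, 50% closure by Day 42 in both arms and α = 0.048. The comparison is dropping the participants against following them to Day 42. Several runs of 1,500 to 20,000 trials gave these ranges:

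| Exclusion (control / NPWT) | Who is excluded | Type I error |
|---|---|---|
| 0% / 1% | non-closers | 4.9% |
| 0% / 2% | non-closers | 5.1–5.8% |
| 0% / 5% | non-closers | 8.3–8.9% |
| 0% / 5% | unrelated to outcome | 4.7–5.1% |
| 2% / 10% | unrelated to outcome | 4.8–5.1% |
| 5% / 5% | non-closers | 5.1% in 20,000 trials |

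For the equal-exclusion row, two smaller runs gave 4.9% and 6.4%. The largest run and the formula in step 3 (4.8%) show no inflation.

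**The case against.** The strongest reply is that this is a familiar full-analysis set, that one valid assessment is enough to stay in it, and that harm requires early loss that is unequal, prognostic and more than trivial. Nothing in the article indicates such loss. That reply stands as a limit on severity. It does not make the ITT label correct.

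A reader might infer more than the document supports:

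- **That patients who switch therapy are dropped.** They are not. Participants are analysed as randomised, and changes of therapy remove them only from the per-protocol set.
- **That many will lack a baseline.** Wound size is a stratification factor, so a size must exist at randomisation. The post-baseline condition matters more. What counts as valid may be defined in the full protocol or SAP, so its absence from the article is not held against it.
- **That the definition by itself distorts the primary test.** For participants with no post-baseline data it does not (step 2). Redefining the set while keeping the censoring rule would leave the log-rank result unchanged for them.
- **That the error rate is known to be large, or to favour NPWT.** The higher figures come from assuming that all losses are non-closers and fall mainly on one arm. Reversing the arms reverses the direction.

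There is also a fair objection to one remedy. Making non-closure to Day 42 the sole primary rule can itself create bias. If early loss is unrelated to prognosis but heavier in control, simulated error under that rule is about 8% (5% control against 0% NPWT) and 13–14% (10% against 2%), nearly all favouring NPWT. Dropping the same patients gives about 5%. That rule therefore belongs in a sensitivity analysis.

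**Conclusion.** The point holds in limited form. The main analysis set is a modified ITT under an ITT label, in a trial where the arm is known, and no all-randomised analysis is described. The direct effect is on the incidence denominators. The primary log-rank test is affected only through participants with follow-up who are removed because an assessment is judged not valid.

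The size cannot be computed from the article. If all those excluded are non-closers, type I error is about 5.5% for 0% against 2% exclusion and about 8–9% for 0% against 5%, compared with a nominal 4.8%. With equal exclusion, or exclusion unrelated to outcome, it is not inflated. This should be fixed, but it does not show that the primary result would be invalid.

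**What to change.** 1. Define ITT as all randomised participants, analysed in the arm to which they were randomised.
2. Include every participant with any follow-up in the log-rank test.
3. In the incidence analysis, count those without a post-baseline assessment as non-closure. This fits the article's carry-forward rule, because the only observation to carry forward is an open wound at baseline.
4. Add a sensitivity analysis of the primary endpoint that keeps those participants as not closed to Day 42. State that this rule can mislead if early loss is unequal and unrelated to prognosis.
5. Report the number excluded, and the reasons, by arm.
6. Keep the present set only as a sensitivity analysis labelled modified ITT.

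The cost is wording, slightly lower estimated closure rates and a little more analysis. No new data are needed, and the stated sample size does not change.

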### Primary endpoint

The primary endpoint of this trial is defined as time (number of days) to achieve complete wound closure in study participants where closure was observed on or before day 42 and was confirmed to have been sustained for a minimum of 14 subsequent days. Complete wound closure is defined as 100% epithelialization, no drainage from the wound, no need for adjuvant therapy or dressing and no presence of sutures. Complete wound closure has to be confirmed after a minimum of 14 consecutive days. The clinically determined primary endpoint will be verified through blinded assessment of wound photos by observers that are independent from the clinical trial.

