### Secondary clinical endpoints

The incidence of wound closure achieved within each treatment arm will be evaluated after a maximum study observation/treatment period of 42 days. These wound closures have to be confirmed as being sustained for a minimum of 14 subsequent days. This will be conducted via blinded photographic analysis. Recurrence of wound opening after initial closure and confirmed wound closure will be assessed and compared between the treatment groups. Reduction of wound size over time will be evaluated using reduction in wound volume and wound surface area over time.

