### Safety endpoints

Incidence of serious adverse events (SAEs) including mortality of any cause within 132 days from the time of initiation of therapy, incidence of device-related events (ADEs), wound-related adverse events (AEs) and incidence of unsustained closure within the study treatment time of 42 days are considered to be safety endpoints of this trial.

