### Setting

This multicenter study will be conducted in abdominal surgical hospital departments with the required manpower as well as structural and scientific qualifications. For both treatment arms, a maximum treatment time of 42 days to achieve complete wound closure shall be provided to cover 80% of participants, whether healing occurs by secondary or delayed primary closure [4]. All participants will be followed up for 90 days (three months) after the maximum treatment time, independent of whether a wound closure was achieved or not, or at which time point within the maximum timeframe for active treatment the wound closure was achieved. Thus, a general follow-up date for all study participants will be at Day 132. A follow-up period of three months after the active treatment period allows for an assessment of recurrence of the wound dehiscence or impairment as well as an adequate assessment of health economic relevant issues. Participants who have not achieved wound closure after 42 days will be seen at 45 days (six weeks) after the end of active treatment time (Day 87). This timeframe allows for a complete assessment of wound progression after study treatment and an assessment of wound closure that is achieved later than Day 42. Figure 1 gives an overview of the study flow. Study therapy will be started on participants in ambulatory care or in hospital and may be continued in ambulatory care. Due to the scope of the trial to evaluate outcomes and benefits of V.A.C.® Therapy when compared to SCWT when used across these care settings, all patients at the time point of randomization or inclusion, or during the active treatment period of 42 days that are eligible for outpatient care and have reasonable access to it, have to be transferred to outpatient care. The transfer of appropriate patients to outpatient care will be monitored and a missing transition that is not due to the medical condition of the patient or the need to provide the optimal treatment will be considered to be a protocol violation.

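### Deaths before closure have no rule of their own in the primary analysis and, on the ordinary reading, are censored as if the wound could still close; LOCF for incidence and recurrence sits badly with the 14-day confirmation

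*Protocol article*

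**What the plan says.** The section *Type of analysis* of the protocol article sets two rules.

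- **Primary endpoint, time to complete closure.** It "will be compared between the two treatment groups using a log-rank test", and *Determination of sample size* adds Kaplan-Meier curves. On missing data: "For the analysis of the primary efficacy endpoint, missing values will be incorporated as censored values". No censoring date is given, and death is not mentioned.
- **Secondary endpoints.** "The last observation carried forward (LOCF) method will be used for the analysis of the endpoints" of incidence of closure, recurrence and wound-size reduction, "in case of study determination or death". The word before death is evidently meant as termination.

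The endpoint definitions require confirmation. Under *Primary endpoint*, a closure by day 42 counts if it "was confirmed to have been sustained for a minimum of 14 subsequent days". Under *Secondary clinical endpoints*, on incidence: "These wound closures have to be confirmed as being sustained for a minimum of 14 subsequent days".

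Follow-up is long and deaths are foreseen. *Setting* states: "Thus, a general follow-up date for all study participants will be at Day 132". *Safety endpoints* includes "mortality of any cause within 132 days from the time of initiation of therapy".

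**The concern.** Kaplan-Meier and the log-rank test treat a censored patient as having the same future chance of closure as those still at risk. For a patient who has died with an open wound this is false. For a patient who leaves because the wound does badly it is doubtful. Neither patient nor physician is blinded (*Blinding*), so exits could differ by arm. If so, the arm that loses more non-healers looks better in the primary test.

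The LOCF rule raises a different problem. A wound last seen closed, in a patient who dies or leaves before the 14-day confirmation, would be carried forward as closed if LOCF takes the last observed state. That inflates incidence and conflicts with the endpoint's own definition. For recurrence, the rule carries an absence of reopening forward over time in which nobody looked. For a wound closed by day 42 this can be up to 132 − 42 = 90 days or more.

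**Working it through.** **1. The plan's own figures** (*Determination of sample size*): control closure 50%, difference 12.5 points, power 80%, α 0.05 (0.048 at the final analysis), maximum loss 10% in both groups.

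With n = [z(1−α/2)·√(2·p̄·q̄) + z(0.80)·√(p₁q₁ + p₂q₂)]² / d² and p̄ = 0.5625:
- α = 0.05, two-sided: (1.960 × 0.7016 + 0.8416 × 0.6960)² / 0.125² = 246.1, against 246 stated.
- α = 0.048: z = 1.977 gives 249.1, against 249 stated.
- Loss: 498 / 0.90 gives 554 and 498 × 1.10 gives 548, against 550 stated.

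The figures reproduce. The point below does not change them.

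**2. Size of the Kaplan-Meier overstatement.** Exit rates, timing and prognosis are not in the documents. Assume that all leavers would never have closed. If a share x leaves before any closure occurs, the estimate becomes p / (1 − x). That is an upper bound for this assumption:
- p = 50%, x = 5%: 0.50 / 0.95 = 52.6%.
- p = 50%, x = 10%: 0.50 / 0.90 = 55.6%.

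Simulation with later exits gives less:

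| True closure | Exits | Exit days | Day-42 Kaplan-Meier |
|---|---|---|---|
| 50% | 5% | 1-41 | 51.9% |
| 50% | 10% | 1-41 | 53.7% |
| 50% | 10% | 1-14 | 54.7-54.8% |
| 62.5% | 10% | 1-41 | 67.5% |

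Keeping the leavers at risk to Day 42 returns the true 50% and 62.5%.

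**3. Size of the test bias.** Simulated with no true effect, 50% closure in both arms and a two-sided log-rank test at 0.048. Most runs used 249 per arm with exponential closure times. One used 275 per arm with closure uniform over days 7-42 and exits on days 1-41. Ranges cover these variants.

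| Exits, control / NPWT | Who leaves | Rejection, exits days 1-14 | Rejection, exits days 1-41 |
|---|---|---|---|
| 10% / 10% | all never-closers | 5.0% | 5.5% |
| 5% / 10% | all never-closers | 7.7-9.6% | 7.0% |
| 0% / 10% | all never-closers | 15.0-18.4% | 8.4-11.9% |
| 5% / 10% | half forced never-closers, half random | 5.0% | 4.8% |

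For 0% / 10% with half the leavers forced to be never-closers and half random, rejection is 6.2-7.8% across runs and exit timings. With all leavers never-closers, holding exits at risk to Day 42 brings rejection to about 4-6%. In the half-and-half case it helps little (6.6-7.3%), because some of those held as not closed would in fact have closed. With only a few deaths (2% / 4%, all never-closers) rejection is 5.6-5.9%.

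**4. LOCF and incidence.** Each 1% of an arm that exits closed but unconfirmed adds 1 point to incidence if the observed state is carried. At the planned maximum loss of 10% the possible range is 0 to +10 points in an arm, against a planned difference of 12.5 points. Where in that range the trial would fall cannot be told from the documents.

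**The case against.** **The wording is open.** The primary rule names neither death nor a censoring date, and the article condenses a fuller document. A reader might infer that the protocol prescribes censoring deaths at exit. It does not say so. What stands is that censoring is the only primary rule stated, that no other section handles death, and that censoring at last observation is what the rule ordinarily means.

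**LOCF may carry the confirmed state.** A reader might conclude that the plan counts unconfirmed closures. The incidence endpoint is itself defined by confirmation, so carrying its own status forward would give not closed. The text does not say which status is meant. This is a conflict on the literal reading, not an established breach.

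**The two rules need not contradict each other.** They govern different endpoints. The chi-squared analysis already counts a leaver with an open wound as not closed, so it partly serves as a check on the primary result. That is a fair credit, apart from closures that were seen but never confirmed.

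**Stopping therapy is not leaving.** Patients are analysed as randomised whatever treatment they received, and all are to be followed to Day 132. Early censoring arises only when observation itself stops. This should keep the number of affected patients down, but it does not help with deaths.

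**The larger error rates are worst cases.** They need leavers who would never have closed and exits that differ by arm. They are highest when exits come early. The plan assumes a maximum of 10% loss in both groups, and with equal exits the test keeps its level. All of this stands, and it limits the severity.

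**Conclusion.** The point holds as a defect in stated rules that should be fixed. On the ordinary reading, a death with an open wound leaves the risk set as if closure could still follow, and this overstates Kaplan-Meier closure. If all leavers are never-closers, the overstatement is about 2-5 points at 5-10% exits. That assumption is exact for deaths before closure and a worst case for live drop-outs.

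Bias in the primary test needs exits that differ by arm. A 0% versus 10% imbalance of never-closers gives roughly 8-16% rejection instead of about 5%, with some variants reaching 18%. If only some leavers are non-healers the excess is much smaller, and with equal exits there is little or none.

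It would be tempting to say that the primary test is inflated or favours NPWT. The documents give no exit rates, timing or prognosis by arm, so neither the presence nor the direction of such a bias can be claimed.

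The LOCF rule must be reconciled with the 14-day confirmation, and it is weak for recurrence because it fills unobserved time with a favourable state.

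**What to change.** 1. **Primary analysis, deaths.** Keep a participant who dies before confirmed closure at risk as not closed, censored at Day 42. This matches treating death as a competing event on the cumulative-incidence scale. A cause-specific log-rank test would simply censor at death again, so the wording should be explicit.
2. **Primary analysis, live drop-outs.** Keep censoring at last assessment and say so. Add a sensitivity analysis in which every exit without confirmed closure counts as not closed to Day 42. Do not sort drop-outs by reason: in an unblinded trial that judgement could itself introduce bias.
3. **Incidence.** Replace LOCF by the rule that a closure without 14-day confirmation is not a closure.
4. **Recurrence.** Replace LOCF, for example with the proportion of all randomised participants whose wound closed and was still closed at Day 132. This keeps the randomised comparison, which an analysis restricted to closers does not.

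The cost is wording in the analysis plan, settled before unblinding, and reliable dates of death and last assessment. Reported closure rates become slightly lower. The sample size does not change.

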### Intervention and comparison

This study is designed to evaluate treatment effects of a medical device in comparison to control therapy. Trial intervention is wound treatment with V.A.C.® using the basic principle of NPWT (Figure 2). The V.A.C.® therapy system is a non-invasive wound therapy system that uses controlled, localized negative (that is, subatmospheric) pressure to create an environment that promotes wound healing in chronic and acute wounds. The V.A.C.® therapy system label has been on the market since 1995 and bears the CE mark and includes the trade name and address of the manufacturer, the batch code, and all other essential information according to European Union (EU) Directive 1993/42/EEC. The V.A.C.® therapy system promotes wound healing through optimization of blood flow, decreasing local tissue edema, and removing excessive fluid from the wound bed. These physiologic changes facilitate the removal of bacteria from the wound. Additionally, the cyclical application of subatmospheric pressure alters the cytoskeleton of the cells in the wound bed through microstrain, triggering a cascade of intracellular signals that increases the rate of cell division and subsequent formation of granulation tissue. Moreover, this system has been shown to also cause macrostrain, bringing the edges of the wound closer and also stimulating wound bed granulation. [11] The V.A.C.® therapy devices that will be used in this study include the ActiV.A.C.® Therapy System, InfoV.A.C.® Therapy System, V.A.C. Freedom® ,V.A.C. Via® and V.A.C. Ulta® Therapy Systems. All V.A.C.® Therapy devices to be utilized in this study bear the CE mark and will be operated within normal conditions of use. In addition, all dressings to be used in the treatment group (V.A.C.® Therapy) bear the CE mark and will be used according to clinical guidelines. The use of the allocated V.A.C.® Therapy System should be performed according to the clinical guidelines released by KCI. Devices can be used with the black GranuFoam™ Dressing, V.A.C. GranuFoam Silver® Dressing, or V.A.C.® White Foam Dressing as indicated by the treating physician. Dressing changes are recommended to be performed every 48 to 72 hours, no fewer than three times per week, with frequency adjusted by the clinician as appropriate. Furthermore any concomitant therapies or procedures deviating from the clinical standard wound treatment or with investigational character (for example, use of hyperbaric oxygen therapy) are not allowed during the course of the trial.

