
**Figure 2 F2:**
[figure not shown]
**Vacuum Assisted Closure (V.A.C.®).** The figure shows the foam dressing fitted into the wound that helps to provide the necessary mechanisms to promote granulation tissue formation. The Sensa T.R.A.C.™ pad regulates pressure at the wound site and the V.A.C.® Therapy Unit provides intermittent and continuous therapy with integrated patient safety features. Copyright by KCI with permission for use for study related publications.

Incidents, complications or adverse reactions like pain during dressing changes, maceration, cellulitis or bleeding, and so on, have been reported only sporadically while using V.A.C.® therapy for treating acute and chronic wounds. Potential adverse events can usually be avoided or significantly reduced by complying with the basic rules of vacuum therapy (as detailed in the manufacturer’s instructions for use and guidelines for the use of V.A.C.® Therapy) as well as by the use of specifically designed vacuum device systems [32-34].

Control therapy is defined as any standard conventional wound therapy (SCWT) according to local clinical standards. Standard therapy is defined as the currently accepted and widely used treatment for the respective wound type, based on the results of past research. Therapy options for standard wound care are treatments that experts agree to be appropriate, accepted, and widely used. Health care providers are obligated to provide patients with best practice and standard of care.

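### The per-protocol analysis deletes anyone with any deviation; because deviations during treatment accrue mainly while the wound is open, deletion removes slow healers and can bias this secondary comparison if the arms deviate at different rates

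*Protocol article*

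**What the plan says.** The main analysis is ITT, with time to complete closure compared by log-rank test. As a secondary approach, Type of analysis states that "a per protocol (PP) analysis will be performed without patients with any protocol deviations". The listed deviations are of two kinds:

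- **Fixed at baseline:** eligibility violations, the first item in "Violations of inclusion and exclusion criteria; changes of randomized therapy".
- **Arising after randomisation:** "changes of randomized therapy; the use of concomitant therapies or procedures deviating from the clinical standard wound treatment", and lapses in the dressing schedule: "dressing changes not performed as recommended to be performed every 48 to 72 hours (no fewer than three times per week) will be considered as" deviations.

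The rule has no time limit or severity threshold, and it does not censor at the deviation.

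Three other statements bear on it:

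- Primary endpoint: closure requires "no need for adjuvant therapy or dressing and no presence of sutures".
- Setting: in both arms "a maximum treatment time of 42 days to achieve complete wound closure shall be provided".
- Intervention and comparison: the interval appears in the description of the V.A.C. regimen ("Dressing changes are recommended to be performed every 48 to 72 hours, no fewer than three times per week"). For the other arm, "Control therapy is defined as any standard conventional wound therapy (SCWT) according to local clinical standards", with no interval given.

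**The concern.** A closed wound has no dressing change to miss and essentially no randomised therapy to switch. A wound closed on Day 10 is at risk of such a deviation for about 10 days; one that never closes is at risk for 42. Deleting every participant who deviates therefore selects on the outcome being analysed, even when deviations have nothing to do with healing.

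Within each arm this inflates the closure rate among those kept. Between arms it matters when deviation rates differ, because the arm with more deviations keeps a set more enriched for closers. Different rates are plausible here: the interval is written for the device regimen, while control follows local practice. If the interval is counted only in the V.A.C. arm, the bias favours V.A.C. If local control schedules are also judged against it, the bias could favour control. The article does not say which applies.

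At stake is how the per-protocol result can be read. Under this rule, neither agreement nor disagreement with ITT is informative.

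**Working it through.** **The plan's own figures.** For 50% v 62.5% and 80% power (two-sided, no continuity correction):

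n = [z(α/2)·√(2·0.5625·0.4375) + 0.8416·√(0.5·0.5 + 0.625·0.375)]² / 0.125²

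This gives 247 per group at α = 0.05 (246 stated) and 250 at α = 0.048 (249 stated). Allowing for 10% loss, 498/0.9 = 553.3, so 554 (550 stated). The inputs reproduce to within rounding. The article gives no figure for the per-protocol set.

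**Inputs from the article.** 50% closed by Day 42 in control, follow-up cut at Day 42, log-rank test, final α = 0.048, and 550/2 = 275 per arm.

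**Assumptions.** No true effect (50% in both arms), exponential closure times, and deviations unrelated to healing that occur at a constant weekly probability w while the wound is open. The article gives no value for w, so a range is shown.

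**Deletion depends on open time.** With an assumed 2% lapse per dressing change and three changes a week, a wound closed at two weeks (6 changes) is deleted with probability 1 − 0.98⁶ = 11%. One open to Day 42 (18 changes) is deleted with probability 1 − 0.98¹⁸ = 31%.

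**Closure rate among those kept.** Let λ = ln 2/42 = 0.0165 per day and h = −ln(1 − w)/7.

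- Closed and kept: a = λ/(λ+h) · [1 − exp(−42(λ+h))]
- Open at Day 42 and kept: b = exp(−42(λ+h))
- Deleted: 1 − (a+b). Closure rate among those kept: a/(a+b).

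For w = 5%: h = 0.00733, a = 0.438, b = 0.368. Deleted is 1 − 0.806 = 19%, and apparent closure is 0.438/0.806 = 54.4% against a true 50%. In the same way:

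| w per week | deleted | closure among kept |
|---|---|---|
| 2% | 8% | 51.7% |
| 3% | 12% | 52.6% |
| 5% | 19% | 54.4% |
| 10% | 35% | 59.1% |
| 15% | 47% | 64.1% |

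**False-positive rate after deletion** (simulation, 275 per arm, nominal 4.8%; differences from the table above):

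| weekly rates | deleted | false closure difference | log-rank rejects |
|---|---|---|---|
| 5% v 5% | 19% v 19% | 0 | about 5% |
| 3% v 5% | 12% v 19% | 1.8 points | about 6–7% |
| 2% v 5% | 8% v 19% | 2.7 points | about 10% |
| 5% v 10% | 19% v 35% | 4.7 points | about 19% |
| 5% v 15% | 19% v 47% | 9.8 points | about 55% |

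If the interval counts in one arm only (runs with 249 per arm), 2% v 0% rejects in about 7%, 5% v 0% in 17% and 10% v 0% in 54%. Swapping the arms in the last case gives the same 54% in the opposite direction.

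**Comparison methods on the same data.** ITT stays at 4.5–5.2%. Keeping everyone and censoring at the first deviation stays within 4–6%. Deleting the same shares independently of outcome gives about 4.8%, so selection on open time causes the inflation, not the loss of numbers.

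**The case against.** Several objections have force.

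- **Not every listed deviation depends on open time.** Eligibility violations are fixed at baseline. Non-standard concomitant therapy is barred throughout the trial, with follow-up to Day 132, so it can occur after closure. This stands: the point covers dressing lapses and, largely, changes of therapy.
- **The rates are assumed, and large effects need large imbalances.** At 5% v 20% per week the rejection rate is about 88%, but 57% of one arm is then deleted against 19% of the other, and the population counts would expose that. At 3% v 5% little happens. This stands, so the deleted shares are shown beside each result and the extreme case carries no weight.
- **The size depends on when deviations occur.** A centre whose routine interval differs from the listed one would deviate almost at once. With deviations placed in week 1, deleting 33% v 19%, 44% v 19% and 54% v 19% gives rejection rates of only 4.4%, 6.6% and 11.8%. This stands too.
- **Censoring is not a clean cure.** If slow healers deviate more (a log-normal frailty simulation at 5% v 10% to 20%), censoring rejects in about 10–25% of null trials. Deletion rejects in 41–97%, so censoring remains the better choice.
- **The analysis is secondary.** No alpha or success claim rests on it.

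A reader might infer that the trial's main conclusion is compromised, or that the rule is bound to favour the device. The article supports neither. ITT keeps participants whatever deviations they have, and the direction depends on which arm deviates more, which the text leaves open.

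**Conclusion.** The point holds for the secondary per-protocol comparison and for deviations that accrue during treatment. The article itself fixes the deletion rule, so this is not a detail left to the statistical analysis plan. Deletion raises apparent closure within each arm. It creates a false between-arm effect only if deviation rates differ, which the text makes plausible but does not establish.

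Under constant weekly rates, the false-positive rate runs from just above nominal for a small imbalance, through about twice nominal (10%) at 2% v 5%, to 19% at 5% v 10% and about 55% at 5% v 15%. These figures rest on assumed rates and on deviations unrelated to healing. Early clustering shrinks them; more deviations among slow healers enlarge them.

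**What to change.** Rewrite the per-protocol rule as follows:

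1. Exclude participants only for violations fixed at baseline (eligibility).
2. For listed deviations after randomisation, keep the participant and censor time to closure at the first deviation.
3. Take per-protocol closure incidence at Day 42 from the Kaplan-Meier estimate with the same censoring, instead of a chi-squared test on the retained set.
4. Report the number and timing of censorings by arm, and state whether the dressing interval counts as a deviation in the control arm.
5. Adjust for, or weight by, baseline wound size and centre, and describe the per-protocol result as supportive only.

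The cost is wording in the protocol and analysis plan, plus a date for each deviation; Data Quality Assurance already provides for full source data verification. The downside is that censoring assumes the deviation is unrelated to prognosis. Step 5 can reduce that problem only as far as wound size and centre explain it.
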